# Measuring the effect of nurse practitioner (NP)-led care on health-related quality of life in adult patients with atrial fibrillation: study protocol for a randomized controlled trial

**DOI:** 10.1186/s13063-017-2111-4

**Published:** 2017-08-03

**Keywords:** Atrial fibrillation, Health-related quality of life, Nurse practitioner, Sustainable models of healthcare, Patient satisfaction

## Abstract

**Background:**

Atrial fibrillation (AF) is a common arrhythmia associated with significant morbidity, mortality, and healthcare resource use. The prevalence of AF is increasing with a growing and aging population, and timely access to care for these patients is a concern. Nontraditional models of care delivery, such as nurse practitioner (NP)-led clinics, may improve access to care and quality of care, but they require formal assessment. The objective of this study is to assess the effect of NP-led care on the health-related quality of life (HRQoL) of adult patients with AF.

**Methods/design:**

We plan a randomized controlled trial comparing NP-led care vs. standard care. Inclusion criteria are ≥18 years of age, documented nonvalvular AF, willingness to give informed consent, and capacity to complete questionnaires. Patients referred for electrophysiological intervention who are clinically unstable or unable to attend follow-up visits will not be eligible to participate. Patients will be asked for verbal consent during the initial triage phone call from the nurse. Randomization will occur via a secure website. The intervention includes an NP consult, including medical history, physical examination, patient teaching, treatment plan, and follow-up at 3 and 6 months. The control arm involves usual cardiologist consultation with follow-up determined by the cardiologist’s practice pattern. The primary outcome will be the difference in change in Atrial Fibrillation Effect on Quality of Life Survey scores at 6 months between groups. Secondary outcomes will include difference in change of EQ-5D scores at 6 months between groups, difference in composite outcomes of death resulting from cardiovascular cause, hospitalizations and emergency department visits between groups, and satisfaction with NP-led care measured by the Consultant Satisfaction Questionnaire. A sample size of 70 per group will ensure adequate power despite a potential 10% loss to follow-up.

**Discussion:**

Our study will determine the effect of NP-led AF care on HRQoL in patients with AF, as well as measure its impact on relevant outcomes such as death, hospitalization, and emergency department visits. Our findings may have implications for delivery of care to patients with AF.

**Trial registration:**

ClincalTrials.gov, NCT02745236. Registered on 16 April 2016.

**Electronic supplementary material:**

The online version of this article (doi:10.1186/s13063-017-2111-4) contains supplementary material, which is available to authorized users.

## Background

Atrial fibrillation (AF) is the most common arrhythmia, and it is increasing in prevalence in a growing and aging population [1]. Currently in Canada, there are approximately 350,000 people living with AF [2], but this number is expected to rise. Many countries are experiencing a healthcare crisis, including Canada [3–5]. Increasing healthcare demands in an already overwhelmed system require new methods of care delivery to be examined.

AF is a chronic disease associated with devastating complications such as stroke and heart failure [6]. Patients with AF have a three to five times greater risk of stroke, with strokes typically larger and associated with higher mortality than in patients without AF [1]. There are evidence-based guidelines for treatment for AF in Canada [6] that promote evidence-based practice and improved patient outcomes, including improved quality of life (QoL) and symptom control. Early intervention and individualized assessment are fundamental for optimal AF management.

Currently, healthcare in Canada comprises more than 40% of all government funding [7], and these costs are judged to be unsustainable [8]. Estimates indicate AF hospitalizations cost the Canadian healthcare system $815 million, with most costs driven by poorly managed AF [9]. In addition, projections suggest that there will be a dramatic inability to meet the future demand for healthcare traditionally provided by a physician [10]. These fiscal and demographic realities support the need for evaluation of new models of care.

Nurse practitioners (NPs) are highly trained clinicians and independent healthcare professionals who work in collaboration with other members of the healthcare team to manage a patient’s full spectrum of healthcare needs [11]. In Alberta, “NP” is a protected title whose scope of practice is legislated pursuant to the Health Professions Act. NPs provide comprehensive health assessment, as well as diagnose, treat, and manage disease, within a holistic model of care [11]. Each NP is accountable for determining his or her own expertise level in specific competencies and when it is appropriate to be involved or refer patients to other healthcare providers [12].

Patients are often more satisfied with NP-led care than with physician-led care [13, 14]. This may be related to NPs’ spending more time engaging with patients in individualized treatment options through patient education and counseling [15]. NP patient-centered care may improve adherence to treatment plans [16–18]. NP care also may improve clinical and patient-reported outcomes as well as lead to substantive cost savings [19–30]. However, despite potential advantages, there are often barriers to broad adoption of NP-led care in many environments [31].

To the best of our knowledge, there has been one only randomized controlled trial (RCT) to date involving assessment of nurse-led care vs. standard physician care for patients with AF. Researchers at a Dutch outpatient hospital clinic randomized 714 patients with AF into 2 equal groups for 2 years [32]. The control arm included a 20-minute initial cardiologist consult and 10-minute follow-up appointment as required. The intervention arm comprised an initial consultation in the nurse-led clinic with diagnostic testing completed prior to the visit. Treatment was guided by AF-specific decision support software. At the end of the consult, a cardiologist would review the patient and care plan. Follow-up visits were held at 3, 6, and 12 months and then every 6 months thereafter. The primary endpoint, a composite of cardiovascular hospitalization and cardiovascular death, occurred in 14.3% in the nurse-led care group compared with 20.8% in the usual care group (HR 0.65, 95% CI 0.45–0.93, *p* = 0.017). Cardiovascular death occurred in 1.1% of the nurse-led care group vs. 3.9% in the usual care group (HR 0.28, 95% CI 0.09–0.85, *p* = 0.025). Cardiovascular hospitalization occurred in the 13.5% in the nurse-led care group vs. 19.1% in the usual care group (HR 0.66, 95% CI 0.46–0.96, *p* = 0.029). Adherence to clinical guidelines was significantly higher in the nurse-led care group. The researchers concluded that nurse-led care for patients with AF was superior to usual care provided by a cardiologist in this setting. Some important limitations of the study were that complex patients were excluded from participating, and a cardiologist was still required to review the patient’s care. Important remaining questions include whether other outcomes are improved, such as health-related quality of life (HRQoL), the patient’s perception of the quality of care received, and whether a more independent practitioner such as an NP would achieve similar results in patients. The objective of this study is to assess the effect of NP-led care on the HRQoL of adult patients with AF.

## Methods/design

We hypothesize ambulatory patients with AF whose care is managed by an NP will have improved HRQoL as measured by Atrial Fibrillation Effect on QualiTy of life Survey (AFEQT) scores compared with patients receiving standard care.

### Design and setting

We propose a prospective RCT with two equal groups testing for superiority (*see* Fig. 1). The RCT will be conducted in the Cardiac Ensuring Accessed and Speedy Evaluation (EASE) Clinic, a multidisciplinary general cardiology outpatient referral clinic in a large tertiary care hospital in Alberta [33]. The clinic’s normal practice is for patients to be triaged by registered nurses (RNs) who follow algorithms based on American Heart Association and Canadian Cardiovascular Society (CCS) guidelines. Diagnostic testing is completed prior to the initial clinic visit to decrease time to follow-up. Patients are assessed in the clinic either (1) by an RN or a doctor of pharmacy and a cardiologist or (2) solely by an NP. Follow-up, if required, is either in the cardiologist’s own clinic or the NP clinic. Patients who do not require follow-up will be returned to their family physician’s care. The hospital uses an electronic medical record that incorporates scheduling of diagnostic testing, clinic appointments, and communications (letters, patient’s health history). In the context of this study proposal, *standard care* refers to regular clinic processes as described above.

**Fig. 1 Fig1:**
[figure not shown]
Patient flow diagram. AFEQT Atrial Fibrillation Effect on QualiTy of life survey, EASE Ensuring Accessed and Speedy Evaluation, ER Emergency room, GP General practitioner, NP Nurse practitioner, RN Registered nurse

### Study population

All adult patients who are referred for assessment for AF to the EASE clinic will be asked to participate in the study. Inclusion criteria are patients aged 18 years or older, with documented AF, able to provide informed consent, and able and willing to complete the study questionnaires on their own or with assistance.

Exclusion criteria are patients referred for atrioventricular node ablation or pulmonary vein isolation, patients who have failed rate control or antiarrhythmic medications, or patients who have moderate to severe mitral or aortic valvular heart disease. Patients with unstable AF or who cannot or are unwilling to attend follow-up appointments are also excluded. Study criteria will be reviewed with Cardiac EASE RNs on an ongoing basis to assist with study recruitment.

After verbal consent is obtained during the telephone triage call, the RN will randomize patients on a secure website. Block randomization (using variable block sizes) will be used to ensure there are equal participants in the intervention and control groups and to further conceal allocation. The patient will be scheduled in the determined clinic within 4–6 weeks from the date of referral, consistent with CCS guidelines.

Prior to the initial clinic visit, written consent will be obtained by a research assistant along with the baseline questionnaires. Questionnaires will also be completed at 3- and 6-month in-person follow-up appointments. Patients who are not being seen in follow-up will have the questionnaire mailed to them. Patients will receive telephone reminders in 2 and 4 weeks if the questionnaires have not been returned.

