### Outcomes

The primary outcome is the difference in change in AFEQT scores from baseline to 3 months and 6 months between the intervention and control groups. AFEQT is an AF-specific questionnaire [37] for use with patients with any type of AF. AFEQT is a simple survey with 20 questions based on a 7-point Likert scale covering 3 domains. The questionnaire should take about 5 minutes to complete. Four questions assess AF-related symptoms, eight questions evaluate daily functioning, and six questions evaluate AF treatment concerns. Two questions assessing satisfaction with treatment are not included in the overall score. Questions 1–18 are included in the overall scoring of the questionnaire. A score of zero corresponds to complete disability, whereas a score of 100 corresponds to no disability. The AFEQT has been shown to have good reliability, test-retest reliability, construct validity, and responsiveness as well as discriminatory properties between clinically different groups [37]. The lowest global score is associated with the patients with severe symptoms related to AF. The AFEQT has also been shown to be responsive to change [37].

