All sociodemographic and clinical characteristics for the intervention (NP-led care) and control groups at baseline will be summarized using mean ± SD for continuous variables and the observed counts and percentages for categorical variables. For the main outcome, analysis of covariance (ANCOVA) will be used to assess change in AFEQT scores over time: baseline to 3 months and 3 months to 6 months (repeated dependent measures) in both the intervention and control groups. ANCOVA assumes normal distribution of the data as well as homogeneity of variance and the groups being balanced. Adjustment for pretest scores will identify whether the postintervention difference in scores is truly a result of the intervention. ANCOVA will also account for variation around the posttest means that comes from the variation attributed to the patients AFEQT scores started at baseline. Previously, it has been shown with other HRQoL scores that data can be skewed because of ceiling or floor effects resulting from extreme values and unequal distances between values on ordinal scales [40]. However, the central limit theorem states that the means will be normally distributed regardless of the original distribution when there are at least 30 per group [41]. This study is projected to have 2 equal groups with 70 participants. If the initial data analysis reveals nonnormal distributions and skewed data, further analysis will be completed to determine if transformation of the data is required or if other statistical analysis would be more appropriate. An independent *t* test will be used to assess the difference in means between NP care and physician-led care. Kaplan-Meier survival analysis will be used to evaluate the composite endpoint of cardiovascular death and hospitalizations determined by blinded assessors. Multivariate analysis will be used to adjust for possible differences in baseline characteristics and scores for any significant variables. Consultant satisfaction will be determined by comparing the means with independent *t* tests. A *p* value less than 0.05 will be considered statistically significant. All analyses will be based on the intention-to-treat principle.

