Missing data will be replaced with the overall mean of the missing variable. This technique is known to accurately identify the mean but will underestimate the SD, making the CI overly optimistic [42]; however, other options also have imperfections. This will need to be considered in the final analysis. All analyses will be performed with the latest version of IBM SPSS statistical software (IBM, Armonk, NY, USA).

Data entry will be completed in a mature, secure web application specifically developed for surveys and databases. An application has been specifically designed for this study with limits built into data entry fields to limit errors. Data entry will be completed by [name] with random data entry checks done by a specific Epidemiology Coordinating and Research (EPICORE) Centre staff member. The final dataset will be available only to [name] and a specific EPICORE Centre staff member. We did not feel that a data monitoring committee was needed for the following reasons. First, the NP intervention is already part of how care is delivered at our institution. We are simply evaluating it. Second, because this is a trial of a treatment approach, we did not feel that data monitoring would be necessary (and our research ethics board did not require it).

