### Ethical considerations

This research protocol has been approved by the health research ethics board at the University of Alberta. The patients will be required to read and understand the clinical trial information sheet and provide consent to participate. All patient information and study questionnaires will be treated with confidentiality and locked in a secure data storage facility at the EPICORE Centre (www.epicore.ualberta.ca). All information will be de-identified to maintain confidentiality. Modifications to any part of the study protocol will be resubmitted to the health research ethics board at the University of Alberta. Participants will be notified if applicable.

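### Written consent and the baseline AFEQT follow randomization and booking, so patients may know their arm at both steps, which can bias the primary comparison

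*Protocol article*

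**What the plan says.** The order of events is in the protocol article, Study population:

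1. Verbal consent, then allocation: "After verbal consent is obtained during the telephone triage call, the RN will randomize patients on a secure website".
2. Booking: "The patient will be scheduled in the determined clinic within 4–6 weeks from the date of referral, consistent with CCS guidelines".
3. Written consent and baseline: "Prior to the initial clinic visit, written consent will be obtained by a research assistant along with the baseline questionnaires".

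The abstract also places verbal consent at the triage call. Ethical considerations makes informed consent a condition of taking part: "The patients will be required to read and understand the clinical trial information sheet and provide consent to participate".

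The baseline has two uses. Outcomes defines the primary endpoint from it: "The primary outcome is the difference in change in AFEQT scores from baseline to 3 months and 6 months between the intervention and control groups". The analysis text under Sample size also adjusts for it and relies on that adjustment for the causal claim: "Adjustment for pretest scores will identify whether the postintervention difference in scores is truly a result of the intervention". The same section states: "All analyses will be based on the intention-to-treat principle". For missing values it says: "Missing data will be replaced with the overall mean of the missing variable".

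Blinding is described only for the committee that adjudicates clinical events.

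**The concern.** A baseline covariate protects a randomized comparison because allocation cannot have influenced it. Here it is a self-reported score collected after allocation, in a trial that appears open to patients. Six of the 18 scored AFEQT items concern AF treatment, and the Background and Discussion both argue that patients respond differently to NP care. Expectations about the provider could plausibly colour the answers. If they did so differently by arm, the difference would pass straight into a change score and, in part, into the ANCOVA estimate.

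The second route is selection. A randomized patient who learns the arm can still decline at the written-consent step. Such a patient contributes neither baseline nor outcome. If declining depends on arm and is related to prognosis, those who remain are no longer the randomized groups, and baseline adjustment need not repair that. Overall-mean replacement draws on the patients who did respond, so it cannot recover what the decliners would have reported.

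**Working it through.** **Inputs from the protocol article (Sample size):** difference 12, SD 20, two-sided 5%, 80% power, 64 per arm, 70 per arm recruited, 10% loss to follow-up. **Assumed, because the documents give no figures:** baseline shift, ANCOVA slope, refusal rates, and the outcome gap between refusers and consenters.

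**The plan's own figure.** The normal approximation gives n = 2 × (1.960 + 0.842)² × 20² / 12² = 43.6, so 44 per arm; the exact t-test figure is 45. The stated 64 is not reproduced. It matches a difference of 10 at SD 20, and at 12 points it gives 92% power. That is a separate matter and is noted only because it leaves slack in the power figures below. After 10% loss, 70 × 0.9 = 63 per arm remain: 91.6% power at 12 points, 79.5% at 10.

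**Route 1: baseline shift.** Suppose knowledge of the arm moves one arm's reported baseline by s points and leaves the follow-up score unaffected.

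- Bias of an unadjusted change-score contrast = s. For s = 3, this is 3 points (3/12 = 25% of the MID).
- Bias of ANCOVA = slope × s. For s = 3 and slopes 0.3, 0.5 and 0.7, this is 0.9, 1.5 and 2.1 points (7.5%, 12.5% and 17.5% of the MID).
- For s from 1 to 5, the change-score bias runs from 1 to 5 points and the ANCOVA bias from 0.3 (s = 1, slope 0.3) to 3.5 (s = 5, slope 0.7).

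ANCOVA with pretest adjustment is the method named for the main outcome, so its figures are the relevant ones. The sign depends on which arm shifts and which way.

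**Route 2: arm-dependent refusal.** If a fraction r of an arm declines and decliners differ from consenters by d points, the consenters' mean is off by r × d. With the same d in both arms, the contrast is biased by (r₁ − r₂) × d. The false-positive rates are for a two-sided 5% t test with SD 20, after a further 10% loss.

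| Refusal, one arm / other | n analysed | Bias at d = 5, 10, 20 | False-positive rate |
|---|---|---|---|
| 10% / 5% | 56 / 59 | 0.25, 0.5, 1.0 | 5.1%, 5.2%, 5.8% |
| 10% / 0% | 56 / 63 | 0.5, 1.0, 2.0 | 5.2%, 5.8%, 8.4% |
| 20% / 10% | 50 / 56 | 0.5, 1.0, 2.0 | 5.2%, 5.7%, 8.0% |
| 20% / 5% | 50 / 59 | 0.75, 1.5, 3.0 | 5.4%, 6.7%, 12.1% |

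Equal refusal in both arms gives no bias under this model.

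**Power.** Each 5% refusing removes 0.05 × 140 = 7 patients. With equal refusal of 10% in each arm, 56 per arm remain and power at 12 points is 88.2%; at 20%, 50 per arm remain and power is 84.4%. At the stated inputs, both stay above the planned 80%.

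**The case against.** The strongest reply is that the order is documented but the harm is not. Several parts of this stand.

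- **Verbal consent precedes randomization**, so it would be wrong to infer that patients are randomized without consent. Eligibility also requires willingness to complete questionnaires and excludes those unwilling to attend follow-up, which screens out some likely refusers before allocation.
- **Baseline precedes the first visit**, so the care itself cannot affect it. Only awareness of the arm or selective completion can.
- **Awareness is inferred.** The document does not say patients are told the provider type at booking. Both arms are first seen within the EASE Clinic, so a booking need not reveal it.
- **Size and direction are unknown.** The 3-point shift is an assumption, and a shift could work against NP care as easily as for it.

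A reader might also infer that arm-dependent refusals have already broken the intention-to-treat comparison, or that the plan intends to drop patients who decline. The document supports neither. It reports no refusals by arm and nowhere says that randomized decliners will be excluded. Rules for counting them may sit in a full protocol or SAP that is not shown. The patient-flow and schedule figures are not shown either and may add timing detail.

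What remains is the stated sequence. It leaves both routes open, and no visible text closes them.

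**Conclusion.** The point holds as a risk created by the stated order, not as a demonstrated bias. Written consent and the baseline AFEQT and EQ-5D follow allocation and booking, no blinding of patients or of the research assistant is described, and the AFEQT baseline enters the primary outcome twice. The sequence is certain; patient awareness of the arm is a reasonable inference; arm-dependent answers or refusals are possibilities.

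Under the assumed 3-point shift, ANCOVA would be off by about 0.9 to 2.1 points. Under the assumed refusal patterns, the contrast would be off by 0.25 to 3.0 points. Set against 12 points, neither would create a clinically important difference alone, but the upper end would distort the test noticeably. The issue is validity rather than power. It warrants an amendment because the remedy is cheap: Trial status reports 31 patients enrolled, leaving 140 − 31 = 109 (78%) who could still be covered.

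**What to change.** Choose one of two orders and state it in Study population.

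1. **Conceal until baseline is done.** Randomize at triage as now, but book the patient simply into the EASE Clinic. Do not disclose the assigned provider type to the patient or the research assistant until written consent and the baseline questionnaires are complete. This needs no extra triage time and leaves questionnaire mode and timing as they are. Patients could still decline after allocation, but not because they know the arm.
2. **Consent and baseline first.** Obtain consent and the baseline AFEQT and EQ-5D before the nurse opens the randomization website, keeping the questionnaire mode consistent with follow-up where possible. This closes both routes. It costs some triage time (the protocol puts the AFEQT at about 5 minutes), in a clinic that has already had staffing constraints, and it lengthens the gap from baseline to first visit. A telephone or online baseline would also differ in mode from in-person or mailed follow-up.

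Under either option, state that all randomized patients are counted, say how those who decline written consent enter the analysis, and report post-randomization refusals by arm. Flag patients enrolled under the old order in a sensitivity analysis.

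The cost is a small procedural amendment and resubmission to the ethics board. No change to the sample size is needed for this point.
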